### Sample Size

Sample size calculation for the comparison of the VTE rates in the treatment and control groups is based on a two-sided chi-square test with significance level alpha of 5% and a power of 90%. The pilot study^13^ showed a VTE incidence of 26% in the control group vs 7% in the treatment group. To avoid overoptimistic treatment effect assumptions, we assume VTE rates of 9% and 24% in the treatment and control groups, respectively. This results in 127 patients per treatment group. Assuming a similar dropout rate as in the previous study (approx. 13%), 146 patients per group (292 in total) will have to be recruited (Figure 1).

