**FIGURE 1. F1:**
[figure not shown]
Flowchart of the study.

The analysis of the primary end point will be performed by logistic regression using treatment group and treatment center as covariates because of the stratified randomization with respect to treatment center. The logistic regression analysis provides more power compared with the chi-square test mentioned above. Therefore, the planned sample size calculation is conservative.

An interim analysis of the 2 VTE rates will be performed after recruitment of 50% of patients (n = 146) to adapt sample size if necessary. With respect to the specific history of this scientific project, we assign a high priority to the exclusion of underpowering. The intention of the interim analysis is not to stop the trial early because of futility or efficacy.To be assessed for eligibility (n = 350).To be assigned to the trial, ie, recruited (n = 292).To be analyzed (n = 254).

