### Statistical Analysis

The analysis of the primary end point will be performed by logistic regression using treatment group and treatment center as covariates because of the stratified randomization with respect to treatment center based on the intention-to-treat population. A per-protocol analysis will serve as sensitivity analysis. In addition, according to the very important covariate “duration of surgery” in the previous study^18^ (which could not be used as a stratification variable), an additional logistic regression using treatment group, treatment center, and duration of surgery as covariates will be performed as sensitivity analysis as well.

Analysis of binary secondary end points will be performed in the same way. All secondary variables will be analyzed in an exploratory manner. An interim analysis of the 2 VTE rates will be performed after recruitment of 50% of patients to adapt sample size if necessary (without analyzing futility or efficacy).

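### Adapting the sample size from the two arm-specific VTE rates, with an ordinary logistic regression as the named final test, does not guarantee the 5% two-sided level

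*Protocol article*

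**What the plan says.** The Sample Size section of the protocol article bases the calculation on a "two-sided chi-square test with significance level alpha of 5% and a power of 90" percent. For the rates it says: "we assume VTE rates of 9% and 24% in the treatment and control groups, respectively". It then concludes: "This results in 127 patients per treatment group". Allowing for about 13% dropout, 146 per group are to be recruited.

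The text after Figure 1 sets an interim analysis "after recruitment of 50% of patients (n = 146) to adapt sample size if necessary". It gives the motive as "we assign a high priority to the exclusion of underpowering" and adds: "The intention of the interim analysis is not to stop the trial early because of futility or efficacy". The Statistical Analysis section repeats the plan: "An interim analysis of the 2 VTE rates will be performed after recruitment of 50% of patients to adapt sample size if necessary".

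Both places name the primary analysis as logistic regression with group and center as covariates. Neither attaches stage weights, a combination test or an adjusted critical value. Neither describes the interim look as pooled or blinded.

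**The concern.** The article fixes two things: the information that drives the adaptation (one VTE rate per arm) and the final test (an ordinary regression on all the data). Together they raise a known difficulty. If the final sample size is chosen from the observed interim difference, the weight of each stage in the final statistic depends on the stage 1 result. The ordinary statistic then no longer has its usual null distribution. Early stopping is only one route to a wrong type I error, so ruling it out does not close this one.

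At stake is the primary p-value. The authors hope the result will inform guidelines. A positive result near the threshold could be challenged because the 5% level had not been secured, and that challenge cannot be answered once the arm-specific rates have been seen.

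**Working it through.** **1. Reproducing the planned size.** Inputs from the Sample Size section: rates 0.24 and 0.09, two-sided alpha 5%, power 90%. The mean rate is 0.165.

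n = [1.96·√(2·0.165·0.835) + 1.2816·√(0.24·0.76 + 0.09·0.91)]² / 0.15² = [1.0289 + 0.6589]² / 0.0225 = 126.6, rounded up to **127** per arm.

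Recruitment: 127 / 0.87 = 145.98, rounded up to **146** per arm. Both figures agree with the article.

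**2. Information at the interim.** 146 recruited is 73 per arm, and 73 × 0.87 = 63.5, so about 64 evaluable per arm. This is half of 127.

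**3. Why the level can move without stopping.** Let z1 be the stage 1 statistic, n1 the stage 1 size per arm and n the final size. The normal approximation to the null chance of crossing +1.96 at the end, given z1, is

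1 − Φ[(1.96·√n − z1·√n1) / √(n − n1)].

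Compare the planned size (n = 2·n1) with a doubled size (n = 4·n1):

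| z1 | planned size | doubled size |
|---|---|---|
| 0 | 1 − Φ(2.772) = 0.3% | 1 − Φ(2.263) = 1.2% |
| 1.0 | 1 − Φ(1.772) = 3.8% | 1 − Φ(1.686) = 4.6% |
| 1.5 | 1 − Φ(1.272) = 10.2% | 1 − Φ(1.397) = 8.1% |

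Enlarging the trial after a weak interim result raises the chance of a false positive. Enlarging it after a fairly strong one lowers it. The net effect therefore depends on the rule. Re-powering on the observed rates makes its largest increases when the interim difference is small, which pushes the level up.

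**4. Simulated type I error.** The article gives neither rule nor cap, so these are assumptions: common VTE rate 9%, 16.5% or 24%; 63 or 64 evaluable per arm at the interim; uncorrected chi-square at |z| > 1.96 on all data; at least 1,000,000 trials per scenario.

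| Rule (floor 127 per arm) | Two-sided type I error |
|---|---|
| Fixed design | 4.8-5.0% |
| Re-power upward on observed rates, cap 190 (1.5×) | 5.4-5.5% |
| Same, cap 254 (2×) | 5.7-5.8% |
| Same, cap 508 (4×) | about 6.3% |
| Increase only when IPC looks better, caps 190-508 | 5.1-5.5% |
| Observed control rate, planned rate ratio kept, cap 254 | 4.8-5.1% |
| Increase only if the new size fits within the cap, otherwise 127 | 4.4-4.9% |

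**5. Candidate remedies, same setting.** An inverse-normal test with pre-planned equal weights gives 5.0-5.1% under upward re-powering at each of the three caps. Blinded re-estimation from the pooled rate with the ordinary test gives 4.9-5.0%.

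**6. Power (caps 190 and 254).** The 12%/24% scenario is an assumption chosen to represent a smaller effect.

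| True rates | Fixed 127 | Re-power upward, ordinary test | Same, combination test | Blinded rule, ordinary test |
|---|---|---|---|---|
| 9% / 24% | 90.8% | 97.5-98.8% | 97.2-98.7% | about 93.5% |
| 12% / 24% | about 71% | 86-92% | 84-91% | about 74% |

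The combination test costs about 0.2 to 1.6 points.

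**The case against.** The strongest reply is that this is a condensed article. It never says outright that the final test stays unadjusted after an adaptation, and a full protocol or analysis plan could supply the rule, the cap and an adjusted test. That is fair, and it rules out the stronger reading that the 5% level is definitely broken. The documents do not support that reading: no rule is stated, and step 4 shows arm-rate rules that stay near or below 5%. What stands is narrower. The article itself chose comparative interim data and named the final test, and this pair does not secure 5%.

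A second reply is that large inflation is unrealistic here. This stands in part. A cap of 508 per arm means 1,016 / 0.87, or about 1,168 recruited. With at most 100 patients per center, that needs at least 12 centers, against 292 planned patients. Caps of 1.5 to 2 times are more credible, and there the excess is under one percentage point.

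A reader might also infer that an effect-driven rule defeats the aim of avoiding underpowering because the interim rates are noisy. Step 6 shows otherwise for a rule with a floor of 127: power rises under both scenarios.

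**Conclusion.** The concern holds in a limited form. As described, a sample size adapted from the two arm-specific rates and followed by an ordinary logistic regression does not guarantee the two-sided 5% level, and the absence of efficacy or futility stopping does not change that. Under upward re-powering the level is about 5.4-5.8% with a cap of 1.5 to 2 times the planned size and about 6.3% with a cap of 4 times; other rules leave it near 5%.

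This rests on reading the two rates as one per arm, on about 64 evaluable per arm at the interim, and on an assumed rule, floor and cap. The simulations use a chi-square test in place of the center-adjusted regression, so the last decimal is approximate.

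**What to change.** **Preferred.** Keep the arm-specific re-estimation, and make the primary test an inverse-normal combination of the two stage-wise center-adjusted test statistics: z = √0.5·z1 + √0.5·z2, with weights fixed in advance at the planned 50:50 split whatever the final size. State the re-estimation rule, 127 evaluable per arm as the minimum, and a maximum. Have the interim done by a statistician independent of trial conduct. This retains the sponsor's ability to react to a smaller effect.

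**Alternative.** Re-estimate from the blinded pooled VTE rate with the planned relative effect (24% to 9%) held fixed, the same minimum and a stated maximum, and keep the ordinary test. The cost is that the sample size cannot respond to a smaller effect than planned: power is about 74% if the true rates are 12% and 24%.

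Either is one paragraph of text and adds no procedures. The article reports the trial as not yet under way, and the change must be in place before anyone sees the interim rates.

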### Access to Data

Access to data set will be made available on request.

### Dissemination Policy

The results of the trial will be published according to CONSORT guidelines in peer-reviewed national and international journals, with special emphasis on media relevant to neurosurgeons and angiologists, regardless of the size or direction of the effects. In addition to regular publication in peer-reviewed journals, results will be presented and discussed at national and international neurosurgical and vascular congresses. Data will also be published in the relevant publications of patient support organizations. To increase patient interest and support, we will provide information in lay language through specific publications on our websites, printed flyers, and regular oral presentations at local and national meetings of patient organizations in Germany.^20^

## QUALITY ASSURANCE

The coordinating investigator is responsible for implementing and maintaining quality assurance and quality control systems with written standard operating procedures (SOPs) to ensure that the trial is conducted and the data generated, documented, and reported in accordance with the protocol, GCP, and applicable regulatory requirements.^21^ Monitoring and data reviewing will be done according to a risk-adapted approach by the local Coordination Center for Clinical Trials, which has comprehensive experience managing clinical trials. Tasks assigned to this center will be done according to the written SOPs and German-wide Koordinierungszentrum für klinische Studien Network. Monitoring will be performed by independent CRAs (Coordination Center for Clinical Trials) according to International Council for Harmonisation of Technical Requirements for Registration of Pharmaceuticals for Human Use-GCP E6 and SOP to ensure patient safety, adherence to protocol, and consistency of the data. The monitoring will be done centrally (check of the data entered into the eCRFs) and by means of on-site visits at the respective study center.

Pretrial visits will be carried out by CRAs to assess the suitability of the trial site in terms of facilities and the qualifications and availability of the trial personnel. Based on the prestudy visits, the coordinating investigator will decide whether the site will participate in the study. Teleconferences (each site separately) will be held to coordinate the site prestudy visits for site initiation. The initiation will be supported by Power Point presentations and study materials (investigator's site file, protocol, informed consent, CRFs, etc.) that will be provided to the sites in advance. On-site monitoring at each site is planned by means of regular visits from the beginning to the end of the trial to check the completeness of the patient records, the consistency of the entries in the CRFs, and the compliance with the protocol and GCP. The specific scope of monitoring and source data verification will be specified in the monitoring manual. Each trial site will be monitored shortly after the first subject is enrolled and treated.^22^ Early monitoring will ensure prompt intervention by the clinical research associate or prinicipal investigator in case of problems at the site, such as major inconsistencies in study conduct and CRF completion. A further 7 (average, individual risk-based number depending on recruitment rate and quality of CRF completion) monitoring visits will be made to each site during the enrollment period.^23^ In addition, regular central data monitoring via electronic CRFs will be performed throughout the study to ensure ongoing data quality. Each study site will undergo a close-out visit by the clinical research associate after the last participant at that site has completed follow-up. To ensure data quality and study conduct, the sponsor may conduct site visits by an independent auditor.^24^

## EXPECTED OUTCOMES OF STUDY

Reduction of incidence of VTE.

## DURATION OF THE PROJECT

First patient in to last patient out (months): 24.

Duration of the entire trial (months): 36.

Recruitment period (months): 27.

A timeline of the study is shown in Figure 2.

**FIGURE 2. F2:**
[figure not shown]
Timeline of the study.

## ETHICS

This study will be performed in accordance with the Declaration of Helsinki. A positive ethics vote in favor of conducting the study has been received (Bearbeitungsnummer: 2023-243). All patients are informed in detail beforehand and must provide written consent before participating.

### Data Availability

All data will be made available upon request.
